### Adverse event reporting

The PI will educate the co-investigator and the participants about any AEs that may occur after administration of the study drug, and also instruct them to report all symptoms that may occur after administration. The type, occurrence time, extent, care, treatment medicine, progress of symptoms after using the research medicine, and causal relationship with the study drug should be noted in the CRF. If SAEs occur, the site investigator should notify the Institutional Review Board (IRB) and PI. After receiving the SAE report, the site PI will decide whether the participant should be withdrawn or continue to participate in the clinical trial.

### Sample size calculation

This study was designed based on the assumption that when participants with CHF take OKT, their symptoms would be improved compared to the symptoms of participants who take the placebo. The hypothesis based on this assumption is as follows:
$$ \mathrm{H}0:\updelta =\Delta 1-\Delta 2=0 $$$$ \mathrm{H}1:\updelta =\Delta 1-\Delta 2\ne 0, $$

where:

Δ1 is the average change in VAS score 8 weeks after randomization (within ±3 days) in the OKT group

Δ2 is the average change in VAS score 8 weeks after randomization (within ±3 days) in the placebo group

The sample size calculation was based on the VAS score information of a previously reported clinical trial involving red ginseng [11]. Considering a dropout rate of 20%, we will need to recruit 56 participants in each group to measure the therapeutic effects and to inform the power calculation for a large-scale RCT of OKT in the future.

### Statistical analysis

The basic statistical analysis method will be the degree of change in the efficacy assessment index between the results of the baseline tests performed before the administration of the test drug and the results of the tests at the end of treatment. The statistical significance level will be set at *P* < 0.05. SPSS for windows version 25.0 (IBM Inc., Chicago, IL, USA) will be used for performing the statistical analysis.

#### General characteristics

To test whether the distributions of variables in the test and control groups are homogeneous, an analysis of variance (ANOVA) or non-parametric methods will be used for continuous variables, and chi-squared tests will be applied for categorical variables.

#### Efficacy

For the efficacy assessment, ITT analysis, a method for including all randomly assigned patients in the analysis regardless of violation or dropout, will mainly be used. Per-protocol (PP) analysis, a method which excludes subjects who do not comply with the study protocol or who have missing data, will also be implemented. The missing values of the efficacy assessment variables will be analyzed using the last-observation-carried-forward (LOCF) method.

A paired *t* test will be used for within-group analysis of the primary and secondary outcome variables. Between-group analysis will be performed using repeated measures ANOVA and the paired *t* test for the primary outcome variable. To measure secondary outcome variables, mean changes in the CHH VAS score, the BT, and the results of the WHOQOL-BREF and CST will be assessed. Repeated measures ANOVA and paired *t* tests will be carried out for the CHH VAS score. A repeated measures ANOVA will also be performed for BT. ANOVA and post hoc analyses will be performed for the WHOQOL-BREF results, and a paired *t* test will be used for the CST results. For the analysis of the Questionnaire of Pattern Identification, ANOVA and post hoc tests will be performed, and for the Questionnaire of Cold Hypersensitivity, Cronbach’s alpha and a correlation analysis will be performed.

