#### Withdrawals

Subjects who meet any of the criteria shown in Table 3 will be withdrawn from the study. Reasons for withdrawal will be recorded in a case report form (CRF), and the patient(s)’ data will be analyzed using the intention-to-treat (ITT) method.

**Table 3 Tab3:** Withdrawal criteria for the *Onkyeong-tang* (OKT) clinical trial

Withdrawal criteria	
1. Those whose compliance is less than 70%	
2. Those who become pregnant during the trial period	
3. Those who need surgery or hospitalization due to accidents or other diseases	
4. Patient withdrawal of consent	
5. Those who have used forbidden medicines or treatments such as anticoagulants, psychotropic drugs, or other medications or treatments that may have effects on the symptoms of CHF	
6. Those who need standard treatment because of the aggravation of CHF symptoms	
7. Occurrence of SAEs	
8. Occurrence of other inevitable situations that may make it difficult to continue the trial process 9. Principal investigator’s (PI’s) judgement to discontinue the trial due to some factors affecting the study results	

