##### CST

The purpose of the CST is to measure the temperature recovery ability of both feet after cold stimulation. In this procedure, first the participants will rest for 20 min in a room set at 24 ± 1 °C to allow for stabilization to occur, and then the temperature of both feet will be measured. Next, participants will immerse both feet into a container filled with water at 20 °C for 30 s. Subsequently, their feet will be carefully dried with a towel, and the temperature of both feet will be measured immediately and then 6 min later. The temperature measurement point will remain the same for each foot. BT will be measured using an infrared thermometer (Testo 835-T1). The CST will be conducted at visits 2 and 4. The following is the recovery rate (RR) equation for the CST. The change in RR from baseline will be measured.
$$ \mathrm{RR}=\left({T}_6-{T}_0\right)/\left({T}_{base}-{T}_0\right)\times 100\%, $$

where:

*T*_6_ is the skin temperature 6 min after the CST

*T*_0_ is the skin temperature immediately after the CST

*T*_base_ is the skin temperature at baseline

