However, this study has a few limitations. First, a few participants in this trial are likely to be able to distinguish subtle differences between the placebo and test drugs, because they may have been a participant in similar clinical trials at the recruiting hospital. Second, because CHHF is a disease that is easily affected by cold weather, it is possible that changes in weather may have an influence on the outcomes. Therefore, although the BT measurement and the CST are performed after a relaxation period of 20 min at 24 ± 1 °C in the examination room, warmer weather is likely to produce better results, and colder weather may negatively affect the results. Furthermore, we could not fully exclude other underlying diseases that cause CHHF, because laboratory tests such as the antinuclear antibody (ANA) test could not be performed due to the small size of our research grant. Additionally, because the pathogenesis of CHHF is not clear, all of the CHHF-related diseases are not fully known. Finally, this study sets the criteria for dropout, which may affect the results of this study. For example, those who have used medications or treatments that may have effects on the symptoms of CHF, such as anticoagulants and psychotropic drugs, will be withdrawn. Nevertheless, those who take other medications may have taken them because OKT had not improved their symptoms. As such, when we drop out the subjects with low therapeutic effect, it may influence the results of the study. Nevertheless, efficacy data will be analyzed based on the ITT analysis; therefore, dropout is very unlikely to translate into better results, and in general, the more dropouts, the lower the cure rate. Among the forbidden drugs, anticoagulants were contraindicated, because the body temperature can be increased due to the blood flow-improving effects of anticoagulants. Drugs for hyperthyroidism and antipyretic analgesics were prohibited because they can affect the body’s heat metabolism. Psychotropic drugs were prohibited because they may cause problems related to research ethics. In addition, those whose compliance is less than 70% will be withdrawn. During the clinical trial period, compliance should be monitored to guarantee the power of the study. Compliance data are helpful for the interpretation of trial results to avoid erroneous conclusions and to enrich the value of the results [23]. High levels of non-compliance in a clinical trial may provoke the risk of a type II error (also called beta error or manufacturer’s risk). This is the risk of finding no meaningful difference in drug action between the test drug and control when there is a real difference. Increasing the sample size can reduce this risk; however, it will induce an increase of the expense in trial cost [24]. If the compliance is less than 70%, the effect of the OKT formulation can be lowered, and the result of the study may not be accurate; therefore, those with low compliance will be withdrawn. Poor compliance was also suggested as a dropout criterion in other clinical trials studying PURIAM110 (a dietary supplement) [25], Korean red ginseng [26], and Taeumjowi-tang (a traditional Korean medicinal extract) [27], among others. Other requirements are also proposed as dropout criteria because they may affect ethical issues or research accuracy. Although these criteria may have some impact on the outcome of the study, they were presented to comply with research ethics and to verify the effect of the research medication itself.

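### LOCF in the main ITT analysis can bias the efficacy results in either direction, so the Discussion's assurance about dropout is unsupported

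*Protocol article*

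**What the plan says.** All references are to the protocol article.

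- **Missing data (Efficacy).** "The missing values of the efficacy assessment variables will be analyzed using the last-observation-carried-forward (LOCF) method". No limit is set by variable, visit or reason.
- **Analysis sets (Efficacy).** ITT is described as "including all randomly assigned patients in the analysis regardless of violation or dropout, will mainly be used". The per-protocol analysis is "a method which excludes subjects who do not comply with the study protocol or who have missing data, will also be implemented".
- **Withdrawal (Table 3).** The criteria include "6. Those who need standard treatment because of the aggravation of CHF symptoms". Item 5 covers use of forbidden medicines or treatments. The Withdrawals section keeps withdrawn participants in the ITT analysis.
- **Schedule (Table 4).** VAS is taken at all five visits, so day 28 (visit 3) is the only on-treatment value before week 8 (visit 4). For the cold stress test, "The CST will be conducted at visits 2 and 4", and WHOQOL-BREF follows the same two visits. No early-termination assessment is listed.
- **Assurance (Discussion).** After granting that removing poor responders may affect the results, the text says that "efficacy data will be analyzed based on the ITT analysis; therefore, dropout is very unlikely to translate into better results", and adds "in general, the more dropouts, the lower the cure rate".

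**The concern.** ITT settles who is analysed. It does not settle what value stands in for a missing week-8 measurement, and under this plan LOCF does that. With withdrawal tied partly to symptom course, the carried value can differ systematically from the participant's state at week 8. A treatment failure can then enter the main analysis with the score she had before she worsened.

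The per-protocol analysis offers no check, because it leaves out participants with missing data. If the Discussion's assurance stands, readers may take the main estimate as conservative when its direction of bias is unknown. The trial is a pilot meant to inform a larger one, so a biased estimate would also pass into that trial's planning.

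**Working it through.** **1. The plan's own figure.** Sample size calculation gives 56 per group after 20% dropout. The effect size, SD and power are not in the article, so 56 cannot be rebuilt. Only the dropout step can be checked: 45/(1 − 0.20) = 56.25 and 46 × 1.2 = 55.2, both compatible with 56. Nothing below depends on which was used.

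**2. How many values are affected.** 0.20 × 56 = 11.2, so about 11 per arm. This is an upper bound at the planned rate: follow-up runs to visit 5, and anyone lost after visit 4 already has a week-8 value.

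**3. What LOCF carries to week 8.**

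| Outcome | Last visit attended | Carried value |
|---|---|---|
| VAS | Visit 3 | Day-28 score |
| VAS | Visit 2 | Baseline, change 0 |
| CST, WHOQOL-BREF | Visit 2 or 3 | Baseline, change 0 |

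The last row follows from the schedule alone.

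**4. Bias formula.** With d the proportion imputed in an arm,

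bias = d(OKT) × (carried − true) in OKT − d(placebo) × (carried − true) in placebo.

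If dropout and imputation error are equal across arms, the bias is 0.

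**5. CST and WHOQOL-BREF (assumed values in SD units, improvement positive).**

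- 20% missing in each arm, dropouts like completers: a true difference D becomes (1 − 0.20) × D = 0.8D; for example 0.60 becomes 0.48.
- No true difference, both arms improve 0.5, 10% missing on OKT and 30% on placebo: 0.9 × 0.5 − 0.7 × 0.5 = +0.10, favouring OKT. The reverse imbalance gives −0.10.
- Dropouts truly worsen by 0.5 to 1.0, 30% missing on OKT and 10% on placebo: (0.30 − 0.10) × 0.5 to (0.30 − 0.10) × 1.0 = +0.10 to +0.20, favouring OKT. The reverse imbalance gives −0.10 to −0.20.

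**6. VAS, differential dropout only.** Assumed: SD of change 2, no drug effect, both arms improve 1.0 point between visits 3 and 4, all dropout after visit 3. The carried score is then 1.0 point too high.

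- OKT 10%, placebo 30%: (0.10 − 0.30) × 1.0 = −0.2 points, favouring OKT.
- A 10-point gap in the same direction: −0.1 points.
- SE = 2 × √(2/56) = 0.378.
- Two-sided type I error = P(|Z + bias/SE| > 1.96) = 8.3% for 0.2 points and 5.8% for 0.1, against 5%.

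**7. VAS, failures scored on a better earlier value.** Assumed: SD 2, dropouts truly 1 point worse than baseline at week 8, placebo completers changing by −1.5, OKT completers set so that the true difference over all randomised participants is 0 (−2.21 in the first row).

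| Dropout OKT / placebo | Bias if carried change is −1.0 / −0.5 / 0 |
|---|---|
| 30% / 10% | −0.40 / −0.30 / −0.20 (favours OKT) |
| 20% / 20% | 0 / 0 / 0 |
| 10% / 30% | +0.40 / +0.30 / +0.20 (against OKT) |

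In the first row, for example, (0.30 − 0.10) × (−1.0 − 1.0) = −0.40. In 20,000 simulated trials, that row's false-positive rates in favour of OKT were 17.4%, 11.1% and 7.5%, against a nominal 2.5%.

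**8. The Discussion's reasoning.** That more dropout lowers a cure rate holds when dropouts are counted as failures on a responder endpoint. The Outcomes section lists no such endpoint. The outcomes are continuous, and under LOCF a dropout is scored by her last value, not as a failure.

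**The case against.** **Outcome-related withdrawal is disclosed.** The Discussion names it as a limitation. That stands, but the assurance that follows withdraws the caution on a ground that does not hold.

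**The assurance is hedged.** A reader might infer that the protocol says dropout cannot flatter OKT, or that it derives this from LOCF. It does neither: it calls the outcome very unlikely and cites ITT alone. Since equal dropout with equal imputation error gives no bias, the statement is unsupported rather than shown to be false.

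**Zero change is often conservative.** A reader might take zero change on CST and WHOQOL-BREF as favouring OKT. With equal dropout and dropouts like completers, it attenuates a real difference to 0.8D, in line with the Discussion. It favours OKT only under further assumptions, such as those in steps 5b and 5c of the working (the second and third bullets on these outcomes).

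**The magnitudes rest on assumptions.** None of the SDs, changes or arm-specific dropout rates is in the article. The 5.8% and 8.3% figures model unequal dropout, not failures scored as improvements, and 5.8% is close to nominal. This stands; the figures show possibility and rough scale only.

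**Unseen text may help.** The full protocol may provide an exit measurement, and an SAP may hold sensitivity analyses. Their absence is not part of this point. The main method is nevertheless fixed here.

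**A mixed model is no complete cure.** It assumes missing at random, so unrecorded worsening after a good visit 3 is still modelled from the good value. Multiple imputation for a two-visit outcome gives dropouts broadly completer-like change, which can flatter more than zero does. This stands and shapes the fix.

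**Conclusion.** The point holds in a limited form. LOCF is the stated main method, withdrawal is partly outcome-driven, and the schedule makes the carried value either a day-28 VAS or baseline. Zero change on CST and WHOQOL-BREF for anyone missing visit 4 is certain. The pre-worsening VAS score is possible wherever no exit measurement exists, and Table 4 lists none.

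The direction depends on dropout by arm and by reason, so the documents do not support the stronger reading that LOCF inflates the OKT effect. On the assumed inputs, the VAS bias is 0.1 to 0.2 points for dropout gaps of 10 to 20 percentage points. It reaches 0.4 points, for or against OKT, if dropouts truly worsen and the gap is 20 percentage points. What can be said firmly is that ITT does not justify the claim that "dropout is very unlikely to translate into better results, and in general, the more dropouts, the lower the cure rate". The analysis should be changed, at moderate priority.

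**What to change.** 1. **VAS.** Make the main analysis a mixed model for repeated measures on all observed post-baseline values, with treatment, visit, treatment by visit, visit 2 VAS and hospital, and an unstructured covariance. Report the week-8 contrast as the result.
2. **CST and WHOQOL-BREF.** Use baseline-adjusted ANCOVA with multiple imputation, and report zero change as a sensitivity analysis.
3. **Sensitivity.** Keep LOCF for VAS as a sensitivity analysis. Because items 1 and 2 assume missing at random, add an analysis that assigns an unfavourable value to participants withdrawn for aggravation or forbidden treatment. Fix that value before unblinding. This analysis must accompany the change, since the new main models do not deal with unrecorded worsening.
4. **Discussion.** Delete the assurance about dropout, or qualify it to say that bias may go either way.

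Cost: revised analysis wording, a slightly more complex primary model and a little more programming. No new data or visits are needed, and the SPSS software named in the protocol can fit the model.

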### Randomization

Eligible participants who met the inclusion criteria will be assigned to a treatment group (OKT) or a placebo group with a 1:1 ratio. An independent statistician from the contract research organization (CRO), the Korean Medicine Clinical Trial Center (K-CTC), will perform the randomization. Random assignment numbers will be generated using a web-based randomization system (blockrand package, version 1.3; Intermountain Healthcare, Greg Snow, USA) and will be stratified by hospital. The randomization table of the participants will be retained by the CRO in an opaque sealed envelope throughout the clinical trial period.

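### A paired t test is named as a between-group method for the primary outcome and as the only test for the cold stress test; it cannot compare two independent arms

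*Protocol article*

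**What the plan says.** All references are to the protocol article.

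- **Design.** Randomization: "Eligible participants who met the inclusion criteria will be assigned to a treatment group (OKT) or a placebo group with a 1:1 ratio". Assignment is stratified by hospital. No matching of participants across arms is described.
- **Hypothesis.** Sample size calculation sets H0: Δ1 − Δ2 = 0 against a two-sided alternative. It defines the first term so: "Δ1 is the average change in VAS score 8 weeks after randomization (within ±3 days) in the OKT group". The corresponding mean for placebo is Δ2.
- **Within-group tests.** Efficacy: "A paired *t* test will be used for within-group analysis of the primary and secondary outcome variables".
- **Primary outcome (VAS for cold feet), between groups.** Efficacy, the next sentence: "Between-group analysis will be performed using repeated measures ANOVA and the paired *t* test for the primary outcome variable".
- **VAS for cold hands.** Efficacy: "Repeated measures ANOVA and paired *t* tests will be carried out for the CHH VAS score". The sentence does not say whether these paired tests are within or between groups.
- **Cold stress test.** Efficacy: "a paired *t* test will be used for the CST results". No other test is given for it. The CST is a secondary outcome, measured at visits 2 and 4 and analysed as change in recovery rate.
- **Other secondary outcomes.** Skin temperature gets repeated measures ANOVA; WHOQOL-BREF gets ANOVA with post hoc analyses.

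No independent-samples t test or ANCOVA is named for any efficacy outcome.

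**The concern.** A paired t test works on differences within natural pairs, such as one woman before and after treatment. Between OKT and placebo there are no such pairs. That leaves two ways to carry out the sentence on the primary outcome. One is to pair women across arms arbitrarily, so that the p value depends on how the file is sorted. The other is to test before against after within each arm, which does not address Δ1 − Δ2.

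At stake for the primary outcome is a plan with two between-group methods and no order of precedence. One is invalid, and the other is not pointed at the time point in the hypothesis. At stake for the CST is that a listed efficacy outcome can be reported only as change within each arm. Such change is weak evidence of a drug effect here: the Discussion accepts that weather may influence outcomes and that warmer weather is likely to give better results, even with the stabilisation period before the CST.

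**Working it through.** **1. Which named test addresses the hypothesis?**

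| Outcome | Named tests | Valid OKT-versus-placebo test among them? |
|---|---|---|
| VAS feet (primary) | repeated measures ANOVA; paired t (called between-group) | ANOVA yes; paired t no |
| VAS hands | repeated measures ANOVA; paired t (unlabelled) | ANOVA yes |
| Skin temperature | repeated measures ANOVA | yes |
| WHOQOL-BREF | ANOVA, post hoc | yes, if the factor is treatment |
| CST recovery rate | paired t | none |

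**2. Sample size used in the checks.** The plan recruits 56 per arm and allows 20% dropout: 56 × 0.80 = 44.8, about 45 evaluable per arm. The article gives no effect size, SD or power, so 56 cannot be re-derived. That has no bearing on this point.

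**3. Paired t test forced across arms.** With no true difference and 45 per arm, rejection in 20,000 simulated trials was 4.8% to 5.1%, the same as for the independent t test. The error rate is therefore not inflated. The defects are of another kind.
- The result is not unique. In one simulated data set of 56 per arm, picked because its two-sample p was 0.031, re-sorting one arm's rows 20,000 times gave paired p values whose central 95% ran from 0.014 to 0.057.
- The test cannot be run when arm sizes differ, which is likely in the per-protocol set.

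**4. Paired t test within each arm (the only possible reading with natural pairs, and what the CST has).** Let both arms have the same true mean change, d SD of change, with no drug effect. If p is the power of a one-sample two-sided t test at 0.05, the chance of a significant result in OKT but not in placebo is p × (1 − p).

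| d (assumed) | p, n = 45 | p(1 − p), n = 45 | p(1 − p), n = 56 |
|---|---|---|---|
| 0 | 0.050 | 4.8% | 4.8% |
| 0.2 | 0.259 | 19.2% | 21.5% |
| 0.3 | 0.503 | 25.0% | 24.1% |
| 0.4 | 0.747 | 18.9% | 13.7% |
| 0.5 | 0.907 | 8.5% | 4.1% |
| 0.6 | 0.976 | 2.4% | 0.7% |

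A correct two-sided test errs in OKT's favour 2.5% of the time at every d. The maximum of p(1 − p) is 0.25, at p = 0.5. The documents do not give d.

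**5. Repeated measures ANOVA for the primary outcome.** Simulated with 45 per arm, four visits (baseline, weeks 4, 8 and 12), equal between- and within-subject variance, and 3,000 runs.
- No effect: rejection 5.6% (group by time), 4.7% (group main effect) and 4.5% (two-sample t on week-8 change). All are valid.
- Assumed effect of 0.6 SD of change at week 8 and half that at weeks 4 and 12: power 65%, 43% and 80% respectively.

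**6. Does the independent-groups test alter the sample size?** With 45 per arm and two-sided 0.05, the detectable difference is (1.960 + 0.842) × √(2/45) = 0.59 SD at 80% power, and (1.960 + 1.282) × √(2/45) = 0.68 SD at 90%. Naming the right test does not itself change N.

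**The case against.** The strongest reply is that the sentence on the primary outcome names repeated measures ANOVA first, and that ANOVA compares the arms validly. This stands. A reader might infer that OKT versus placebo is not validly tested at all for the primary outcome. The text does not support that for VAS of the feet, nor for VAS of the hands or skin temperature.

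A reader might also take the paired t tests for VAS of the hands as a second between-group error. They are unlabelled and may simply be the within-group tests announced at the start of the same paragraph. Only the missing label can be criticised.

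Nor does the article adopt a rule that OKT works if its own arm is significant and the placebo arm is not. The hypothesis is between arms, so the percentages in step 4 show what within-arm testing could produce, not what the sponsor plans to conclude. They rest on an assumed common change and fall away above about 0.5 SD. Selection on VAS of 4 or more adds little if visit 2 is the baseline, because eligibility is assessed at visit 1. The weather remark is worded as a possibility; it does not say that weather alone moves the outcome.

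The word for paired may be a slip for independent. That is plausible, but the preceding sentence already gives the paired test to within-group use and this one gives it to between-group use, so the text is wrong as it stands. A fuller analysis plan might settle which ANOVA term matters. On its own that gap would be left to such a plan; it matters here because the ANOVA is the only valid method named for the primary outcome. The reply does not rescue the CST, where the only test stated is paired.

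**Conclusion.** The point holds in limited form. One of the two between-group methods named for the primary outcome is wrong for independent arms and cannot test H0. The other is valid but not tied to week 8. The CST has no valid between-group test. The status of the paired tests for VAS of the hands is unclear.

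For the primary outcome the size is moderate: the valid method exists, and aiming it poorly costs about 15 percentage points of power (80% − 65%) under an assumed effect that peaks at week 8. A different effect shape would give a different figure. For the CST the defect is complete. If its within-arm results were read as efficacy, a misleading contrast would arise in 19% to 25% of null trials with 45 per arm at an assumed common change of 0.2 to 0.4 SD, but in only 2.4% at 0.6 SD. That the paired test is the wrong one for independent arms depends on none of these assumptions.

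**What to change.** In the Efficacy section, or in the analysis plan before unblinding:

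1. For VAS of the feet, replace the between-group paired t test with an independent-groups comparison of week-8 change: ANCOVA with the visit 2 value as covariate and hospital, the stratification factor, as a factor. A two-sample t test is the minimum that corrects the error. Report the difference with its 95% confidence interval.
2. State that this comparison tests H0, and that repeated measures ANOVA is supportive, with group by time as its term of interest.
3. Add the same between-group comparison for CST recovery rate: visit 4 adjusted for visit 2, with its 95% confidence interval.
4. State that all paired t tests, including those for VAS of the hands, are within-group and descriptive and are not evidence of efficacy.

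The cost is a change of wording. No new data, visits or participants are needed.

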### Study design and setting

This randomized, double-blind, multicenter, parallel-group, placebo-controlled pilot study will be conducted at the Korean Medical Hospital of Sangji University and Semyung University Korean Medical Hospital at Chungju and Jecheon.

A total of 112 participants will be enrolled in this study. The study and control groups will have 56 participants each, and the participants will be registered competitively in the three centers. An adequate explanation and time will be given to all participants so that they can make a thoughtful decision before the principal investigator (PI) or researchers obtain written informed consent. Each participant will undergo a screening period 2 to 7 days prior to randomization. During the screening period, the following will be performed: measurement of vital signs, body index (height, weight, and body mass index [BMI]), body temperature, and CHHF Visual Analog Scale (VAS) score; laboratory tests, chest X-ray, and electrocardiogram (ECG); identifying the reason and method of study participation and collecting demographic, sociological, and gynecological information; evaluation of general physical state; Questionnaire of Pattern Identification; and determining if the potential participant meets the inclusion criteria. Those who meet the inclusion criteria will be invited to take part in the study. Subsequently, participants will be randomly assigned to the OKT or placebo group.

After randomization, all participants will be asked to visit the center every 4 weeks for 12 weeks, and the investigational product (IP) will be administered for 8 weeks. One follow-up visit will be conducted 4 weeks after the completion of medication. A total of five visits will be scheduled over the span of 13 weeks. At visits 3 and 4, the participants will be asked to return any IPs not taken for the purpose of calculating drug compliance. Participants will be asked not to take other medications which could affect the CHF symptoms during the trial (e.g., antithrombotic drugs, psychotropic drugs, antidepressant drugs, drugs for hyperthyroidism, functional health foods such as red ginseng, and blood flow-enhancing over-the-counter drugs). The protocol design is based on the Standard Protocol Items: Recommendations for Interventional Trials (SPIRIT) Checklist (see Additional file 1). Figure 1 shows a schematic flow diagram of the study.

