##### WHOQOL-BREF

The WHOQOL-BREF is a questionnaire used to assess quality of life based on 26 items. It consists of five domains: general quality of life, physical health, psychological health, social relationships, and environmental health. The Korean version of the WHOQOL-BREF developed by Min et al. [10] will be used to assess the quality of life of the patients with CHF symptoms at visits 2 and 4.

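### WHOQOL-BREF: the post hoc step has no between-arm contrast with two arms, and ANCOVA on the visit 2 score and hospital would be a free gain in precision

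*Protocol article*

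**What the plan says.** All references are to the protocol article.

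- **Efficacy**, under Statistical analysis: "ANOVA and post hoc analyses will be performed for the WHOQOL-BREF results". The sentence does not name the factor, the response or the contrast that the post hoc tests would examine.
- **WHOQOL-BREF**: the questionnaire "will be used to assess the quality of life of the patients with CHF symptoms at visits 2 and 4", that is, at day 0 and day 56. On its structure: "It consists of five domains: general quality of life, physical health, psychological health, social relationships, and environmental health". The Outcomes section names the total score as the secondary outcome.
- **Randomization**: participants "will be assigned to a treatment group (OKT) or a placebo group with a 1:1 ratio", stratified by hospital. There are three hospitals.
- **Statistical analysis**, opening paragraph: "The basic statistical analysis method will be the degree of change in the efficacy assessment index between the results of the baseline tests" and those at the end of treatment. The Efficacy section also lists WHOQOL-BREF among the secondary outcomes whose mean changes will be assessed.
- **Efficacy** also assigns paired t tests to the within-group analysis of primary and secondary outcomes, and makes ITT with LOCF the main analysis.

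No covariate adjustment is named for WHOQOL-BREF.

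**The concern.** Post hoc tests follow an ANOVA when it compares three or more groups and one wants to know which of them differ. Here there are two. The F test for arm is already the only between-arm comparison, so the post hoc clause either repeats it or refers to something the article does not define. An analyst who follows the sentence has to invent a contrast.

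The second issue is efficiency. Every woman has a visit 2 score, and randomisation is stratified by hospital. Subtracting the visit 2 score is a legitimate use of it but not the most precise one, and hospital is not used at all. WHOQOL-BREF is the trial's only quality-of-life outcome, so the loss is worth avoiding when avoiding it costs nothing. At stake are some precision and an unambiguous statement of the comparison, not the validity of the arm comparison.

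**Working it through.** **1. The plan's own figure.** "Considering a dropout rate of 20%, we will need to recruit 56 participants in each group". Then 56 × 0.8 = 44.8, about 45 evaluable per arm. In the other direction, 44/0.8 = 55 and 45/0.8 = 56.25, which rounds up to 57, so 56 agrees with about 45 evaluable to within rounding. The 45 itself cannot be derived, because the article gives no difference, SD or power. The trial was also sized on the CHF VAS, so this figure says nothing directly about WHOQOL-BREF. It serves here only to set the two sample sizes used below: 45 per arm (evaluable) and 56 per arm (all randomised, as under ITT).

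**2. Post hoc contrasts.** With k groups there are k(k−1)/2 pairwise comparisons. For k = 2 that is 2 × 1/2 = 1, and this one comparison is the ANOVA itself.

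**3. Validity of a two-arm ANOVA.** With two groups F = t². In a test data set of 56 per arm, F and t² were both 2.6868 and both p values 0.1040. In 20,000 simulated null trials per scenario (45 or 56 per arm, ρ = 0.3, 0.5 or 0.7), type I error was 4.6% to 5.4% for ANOVA on change and 4.6% to 5.3% for ANCOVA, against a nominal 5%.

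**4. Precision.** Take SD 1 at both visits and correlation ρ between visit 2 and visit 4 in each arm.

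- Variance of change = 2(1−ρ).
- Residual variance under ANCOVA = 1−ρ².
- Ratio of ANCOVA to change = (1−ρ²)/[2(1−ρ)] = (1+ρ)/2.

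| ρ (assumed) | Change | ANCOVA | Ratio |
|---|---|---|---|
| 0.5 | 1.00 | 0.75 | 0.75 |
| 0.6 | 0.80 | 0.64 | 0.80 |
| 0.7 | 0.60 | 0.51 | 0.85 |

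**5. Power.** Assume a true difference of 0.5 SD and two-sided α = 0.05. The article sets the level at 0.05; two-sided follows its hypothesis for the VAS. The noncentrality is (0.5/√variance) × √(n/2), with 2n−2 degrees of freedom for ANOVA on change and 2n−3 for ANCOVA. For example, at n = 45 and ρ = 0.5:

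- change: 0.5/√1.00 × √22.5 = 2.37, power 65%;
- ANCOVA: 0.5/√0.75 × √22.5 = 2.74, power 77%.

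| n per arm | ρ | Change-score ANOVA | ANCOVA | Gain, points (before rounding) |
|---|---|---|---|---|
| 45 | 0.5 | 65% | 77% | 12.3 |
| 45 | 0.6 | 75% | 83% | 8.8 |
| 45 | 0.7 | 86% | 91% | 5.0 |
| 56 | 0.5 | 75% | 86% | 11.1 |
| 56 | 0.6 | 83% | 91% | 7.2 |
| 56 | 0.7 | 92% | 96% | 3.4 |

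The rows at 56 per arm keep the 0.5 SD difference. With only two measurements, LOCF would carry a dropout's visit 2 score forward to visit 4, which may shrink the difference.

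**6. Hospital.** Three hospitals add two model terms, so the ANCOVA degrees of freedom fall from 2n−3 to 2n−5. At n = 45 and ρ = 0.5 this changes power from 77.29% to 77.26% if hospital explains nothing. Any gain depends on how far scores differ between hospitals, which the article does not say.

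**The case against.** The strongest reply is that nothing here is invalid. A two-arm ANOVA on change is a two-sample t test, the article does use the visit 2 score by subtraction, and ANCOVA is a preference about efficiency. The outcome is secondary, the trial is called a pilot, and a condensed article may leave model terms to the analysis plan. Most of this stands, and it limits the point to low severity. It does not rescue the post hoc clause: the article names a procedure that does not fit its own two-arm design, and an analysis plan that followed it would inherit the problem.

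Three stronger readings are tempting, and the document does not support them.

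- **That the sentence has no valid reading.** It has one, ANOVA on change by arm, and steps 2 and 3 show that it holds its error rate.
- **That the baseline is thrown away, so the right comparison is a visit 4 score alone against ANCOVA.** The Outcomes section does say total score without mentioning change. But the general rule and the Efficacy section both point to change, and change is the fair comparator. Using the visit 4 score alone (65% power at 45 per arm whatever ρ is) would overstate the gain at correlations of 0.6 and 0.7.
- **That the post hoc tests would compare the four arm-by-visit cells as independent groups, giving wrong error terms.** Plain ANOVA here, beside repeated measures ANOVA for other outcomes, may invite that inference. The article states it nowhere, and its paired t tests for within-group analysis show that it treats the two visits as paired.

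Nor does the article say that post hoc means a domain-by-domain follow-up, though a reader might guess so.

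**Conclusion.** The point holds as a free improvement to a secondary outcome, at low severity. The post hoc clause is undefined for a comparison of two arms. The ANOVA is valid when read as an analysis of change, but it carries more variance than necessary: ANCOVA needs 0.75 to 0.85 of it at correlations of 0.5 to 0.7. At a 0.5 SD difference that is worth about 5 to 12 points of power with 45 per arm and about 3 to 11 points with 56, with the smaller gains at the higher correlations. These figures rest on an assumed effect size, an assumed correlation and equal SDs at the two visits, none of which the document gives. The benefit of including hospital cannot be sized from the document.

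**What to change.** Replace the WHOQOL-BREF sentence in the Efficacy section with: the WHOQOL-BREF total score at visit 4 will be compared between arms by ANCOVA, with the visit 2 score and hospital as covariates, and the adjusted mean difference will be reported with its 95% confidence interval. Enter hospital as a three-level factor. Delete the post hoc tests for this outcome.

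The cost is analysis wording only. Both covariates are already recorded, no visit or measurement is added, and the sample size does not change.
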